## Abstract

**Background:**

In Sweden, 72% of people with dementia live in ordinary housing. Of these, 50% receive home care services. Older people with dementia may benefit from developments in decision-making support which aim to facilitate their ability to communicate their personal needs and preferences with care managers and staff in home care services. In this study, we will test and evaluate the use of TalkingMats in Swedish municipal home care services for older people with mild to moderate dementia. TalkingMats is a low-technology communication tool, to help people with communication difficulties express their views. It uses a simple system of picture symbols which are placed on a textured mat. This study will provide insight into the extent to which TalkingMats benefits older people with dementia to feel more involved in decisions related to home care services. In addition, this study will assess the extent to which the use of TalkingMats promotes service providers’ efforts to involve service recipients in decision making. The implementation of TalkingMats in home care services will also be studied.

**Methods:**

A parallel group, two-armed randomized controlled trial design in which TalkingMats and Usual Conversation Method will be compared. Two specific situations where older people with dementia must make decisions about home care services will be studied. First, a follow-up needs-assessment conversation between study participants and care managers will be studied. Second, a conversation between participants and home care staff regarding the delivery of the decided home care services will be studied. In addition, a qualitative approach will be used to gain an understanding of study participant and service provider experiences of the impact and implementation of TalkingMats.

**Discussion:**

The combined exploratory, descriptive, and experimental study design is considered an important strength which will facilitate multi-facetted knowledge production concerning the involvement and communication needs of older people with dementia generally and within the context of home care services specifically. Combining qualitative and quantitative methods will maximize our ability to assess the effects of TalkingMats.

**Trial registration:**

ClinicalTrials.gov ID: NCT05561998. Registered in September 28, 2022.

## Background

In this study we will test and evaluate the use of TalkingMats (TM) as a decision aid in conversations between home care service providers and older people with mild to moderate dementia within Swedish municipal eldercare. In Sweden, approximately 160,000 people live with dementia. In addition, it is estimated that half of the population over 90 years of age live with dementia [1]. In a Swedish study, Odzakovic et al. [2] found that of those with dementia, 72% were living in ordinary housing. Of these, 50% were receiving home care services. In Sweden, when an older person is no longer able to manage daily independent living, they can apply for assistance from the municipal home care services. The extent of the support ultimately provided through home care services is based on a needs assessment. Needs assessments are performed by municipal care managers. If eligible, home care services may include for example help with household chores, personal care, and/or social activities. The purpose of the present study is to increase our understanding of how TM impacts the involvement of older people with dementia in decisions made within the context of home care services.

During the last decade, developments in Swedish eldercare have been dominated by a drive for individualized support with an emphasis on consumer choice [3, 4]. The intent of increased consumer choice being not only to increase choice and control for individuals receiving services, but also to increase the ability to customize services for individual service recipients and increase the quality of the services provided. The Swedish Social Services Act [5] states that eldercare should aim at strengthening older people’s ability to live an independent life, in dignity, and with well-being [4]. Additionally, the Swedish National guidelines on dementia care [1] stipulate that people with dementia are covered by the same policy intentions as other groups using eldercare.

Needs-assessments and conversations about the provision of home care services for older people with impaired cognition are especially challenging [6]. Care managers who conduct needs-assessments and make decisions about home care services often lack training in communicating with people with dementia or other cognitive impairments. In addition, service recipients often lack access to information regarding the services available to them [7]. Home care staff who deliver support often express difficulties with interpreting the wishes of older people with impaired cognition or dementia [8]. In contrast to other countries, Sweden lacks decision-making support for older people making choices about social care [9, 10]. The lack of opportunities for supported decision-making may force service users with the most complex needs into passivity. However, such support may facilitate the ability of older people with dementia to communicate their needs and preferences with home care service providers more clearly [6–8].

Research on people with dementia, using a social perspective focusing on citizenship and rights, has shown that people with dementia, even in advanced stages, can express their wishes and preferences in alternative, more creative ways [11, 12]. In addition, care managers’ behavior in professional encounters with older people with dementia can either promote or constrain self-determination [13]. Studies have found that care managers face several dilemmas in the assessment of the need for support for people with dementia [7, 14]. In addition, families can confuse the best interests of service users with their own interests, which raises questions regarding undue influence [15–17]. Rather than being involved, people with dementia are frequently excluded from decisions about their future care and are often talked about rather than talked to [18, 19]. In such situations, methods to support decision-making may be required. This would allow service users with dementia increased opportunity for choice and control [10, 20, 21] in decisions regarding themselves. A recent meta-analysis of decision aids for older adults showed that decision aids increased knowledge, created more accurate risk perceptions, and helped participants choose options more congruent with their own values [22]. Many of these decision aids were designed as visual aids to be used as conversation props. Even though previous research has shown that such decision support would be welcomed by care managers and other staff in eldercare [7, 8], the use of decision aids when communicating with older people with dementia is extremely limited in Swedish eldercare. This points to the importance of developing and evaluating communication tools and decision aids for use in conversations regarding needs-assessment and of the delivery of home care services.

In this study, we will test TM, an established communication tool, as a decision aid in conversations regarding needs-assessments and the delivery of home care services. In previous research, TM has shown promising results in its ability to support communication with people with dementia. In studies involving people with dementia, TM has been found to positively impact participants perception of involvement in decision-making and choice about things that matter to them [11, 23, 24]. Additionally, TM has been shown to improve participants with dementia's ability to understand conversation topics by providing a visual cue which allows more time to process information [24]. Thus, TM may play an important role in improving quality of care by providing a tool that home care service providers can use to engage with people with dementia and help them express their views about a range of topics [23].

### Aims and research questions

The aim of this study is to test and evaluate the use of TM as a decision aid in conversations regarding needs assessment and the delivery of home care services for older people with mild to moderate dementia within Swedish municipal eldercare. Specifically, this study will provide more insight into the extent to which TM impacts participants perception of their involvement in decision making and the extent to which TM promotes service providers’ efforts to involve service recipients in decision making. Moreover, the process by which TM is implemented into normal municipal eldercare will be studied closely. Using a mix of quantitative and a qualitative designs the following research questions will be answered:

RQ1. To what extent does TM impact participants’ perceived involvement in decision making in conversations regarding home care services compared with usual conversation methods (UCM)?RQ2. To what extent does TM impact service provider efforts to involve participants in decision making in conversations regarding home care services compared with UCM?RQ3. What are the barriers and facilitators of implementing TM as a decision aid in the context of Swedish municipal home care services for older people with mild to moderate dementia?

## Methods

### Design and setting

The present study (Fig. 1) uses exploratory, descriptive, and experimental methods*.* The study will be conducted within the normal operating Swedish municipal eldercare services. The parallel group intervention study is designed as a two-armed randomized controlled trial (RCT) where the use of TM as a decision aid to support involvement in conversations regarding home care services for people with mild to moderate dementia will be evaluated through comparison with UCM. Two different situations where older people with dementia must make decisions about home care services will be studied. The first situation is a needs-assessment conversation between care managers working in eldercare and participants which concerns the follow-up of decisions about home care services. The second situation is a conversation between home care staff and participants regarding the delivery of the home care services chosen during the needs assessment. This study builds upon a previously conducted pilot study (*N* = 10) which aimed to test the intervention, study inclusion criteria, research and practice logistics, and outcome measurements prior to the full effectiveness study described here.

**Fig. 1 Fig1:**
[figure not shown]
Overview over the design of the study

This study will take place within the local eldercare authorities of three municipalities in southwestern Sweden. The largest municipality has just over 100,000 inhabitants and about 22,000 inhabitants aged 65 + . The two smaller municipalities have just under 47 000 inhabitants combined. Approximately 11,000 of whom are aged 65 + . The study will be performed in collaboration between researchers from the Department of Social Work at the University of Gothenburg, the Department of Work Life and Social Welfare at the University of Borås, the School of Health and Welfare at Jönköping University, and managers, research assistants and staff from three municipal eldercare authorities. Continuous meetings and workshops with collaborators will be held throughout the study period, to monitor participant enrolment and adherence to study protocols.

### Recruitment and eligibility criteria

The target group for this study is older people with mild to moderate dementia who use home care services provided by municipal eldercare authorities. Service users will be identified by care managers, healthcare staff or a specialized dementia team. At first contact, potential participants will receive brief information about the study and be offered the opportunity to participate in screening tests for mild to moderate dementia. It will be made clear that the choice to participate in the study (or not) will not affect receipt of eldercare. On expression of interest to participate in the study, permission will be sought by home care service providers to forward contact details to the research team. A research assistant will contact individuals referred to the study to arrange a convenient time to meet. At this visit, written and verbal informed consent will be obtained, and baseline data will be collected.

Eligibility criteria:Participants are aged 65 or older.Participants receive home care services from the eldercare authority in one of the three participating municipalities.Participants are assessed as having mild to moderate dementia which is defined as scoring between 12–23 on the mini-mental state examination (MMSE).

According to preliminary power calculations, we plan to include 50 participants in each study arm. The calculation was made based on what is needed to detect a moderate difference (0.25 effect size) with 0.9 power, p = 0.05 [25]. Significant differences over time in involvement were found using the Involvement Measure Scale (IMS) in a sample of 18 in a previous study [11].

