### Allocation and blinding

Eligible participants will be randomized to either the intervention (TM) or control (UCM) group. The randomization schedule will be developed by a member of the research team not involved in participant recruitment or contact with referring agencies. The randomization sequence will be developed a priori by site (*n* = 3) using the online randomizer random.org with 50% allocation between arms. Results of the randomization for individual participants will be communicated following inclusion and collection of baseline measurement data.

Participants, service providers, and research staff will not be blinded to final participant allocation. Data collection subsequent to baseline measurements will not be blinded.

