### Analysis

Study data will be pooled with pilot data for analysis. To answer RQ1 and RQ2, we will perform descriptive and comparative statistical analyses as well as qualitative thematic analysis [37]. Statistical data analysis methods will be chosen based on data characteristics (e.g., ANOVA, Kruskal–Wallis). Baseline differences between groups will be controlled for in the final analyses. Sensitivity analyses will be conducted (e.g., TOT vs ITT analysis). Methods for handling missing data will be determined based on a missing data analysis to determine the nature of the missingness (e.g., MCAR). Fidelity and implementation will be tested for their impact on results. To check for comparison group equivalence, we will compare the pre-test dementia scores, functional ability and demographic variables of the two groups. When evaluating the video-recordings of the conversations, using the “OPTION scale”, inter-rater reliability will be tested. To interpret the effects of the intervention, qualitative thematic analyses [37] of the participants’ and staff’s experiences as expressed in focus group and individual interview data will be conducted.

For RQ3 we will perform descriptive analyses of survey-data as well as qualitative thematic analysis of focus group and individual interview data. This will provide analysis of patterns and themes in the interview and focus group statements. The qualitative data will enable an analysis of similarities as well as differences in the experiences of the persons involved in the study, on an individual as well as a group level. In addition, a mixed method approach [38] will be used linking descriptive statistics and qualitative analysis.

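### Fifty per arm does not give 90% power for an effect size of 0.25 in this two-arm comparison, under either usual reading of that effect size

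*Protocol article*

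**What the plan says.** The sample-size paragraph is in the Protocol article under Recruitment and eligibility criteria. It states that "we plan to include 50 participants in each study arm" and that this number is what is needed "to detect a moderate difference (0.25 effect size) with 0.9 power", with p = 0.05. The calculation is called preliminary. The effect-size metric, the test, the sidedness, any correlation between repeated measurements and any dropout allowance are not given. The next sentence reads: "Significant differences over time in involvement were found using the Involvement Measure Scale (IMS) in a sample of 18 in a previous study".

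The design around this figure is clear:

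- RQ1 and RQ2 compare TalkingMats (TM) with the usual conversation method (Aims and research questions).
- The trial has two parallel arms (Design and setting), "with 50% allocation between arms" (Allocation and blinding).
- The Involvement Measure Scale (IMS) is collected twice, after the needs-assessment conversation (T1) and after the service-delivery conversation (T2) (Outcome data).
- ANOVA and Kruskal–Wallis are given only as examples of possible tests. Baseline differences will be controlled for, and data from the pilot (N = 10) will be pooled (Analysis; Design and setting).

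**The concern.** Sample size, effect size, power and significance level are all stated, so the claim can be checked, and for two arms of 50 the four numbers are not compatible. An effect of f = 0.25 needs far more than 50 per arm for 90% power, and a standardised difference of 0.25 needs several times more again.

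The IMS sentence does not close the gap. A change over time within 18 people says nothing about the power of a comparison between two independent arms.

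What is at stake is how a null result is read. A trial said to have 90% power for a moderate effect, and that finds nothing, invites the conclusion that TM has no moderate effect on involvement. If the real power is about 70%, the chance of missing such an effect is 30% rather than 10%.

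**Working it through.** **Inputs.** From the document: n = 50 per arm, 1:1 allocation, effect size 0.25, power 0.90, alpha 0.05. Assumed: a two-sided test, since sidedness is not stated. Two readings of 0.25 are taken:

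- Reading A: Cohen's f = 0.25. For two equal groups d = 2f = 0.5.
- Reading B: standardised mean difference d = 0.25.

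**Sample size needed.** The normal approximation is n per arm = 2(z₀.₉₇₅ + z₀.₉₀)²/d², with (1.960 + 1.282)² = 10.507.

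- Reading A: 2 × 10.507/0.25 = 84.1, so 85. The noncentral t gives 86.
- Reading B: 2 × 10.507/0.0625 = 336.2, so 337. The noncentral t gives 338.

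**Power at 50 per arm.** The noncentrality is d√(n/2) = 5d.

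- Reading A: 2.5. The normal approximation Φ(2.5 − 1.96) gives 0.705; the noncentral t gives 0.697.
- Reading B: 1.25. The normal approximation gives 0.239; the noncentral t gives 0.236.

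**Difference detectable with 50 per arm** (noncentral t): d = 0.655 at 90% power and d = 0.566 at 80%.

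**Can the stated figure be recovered another way?**

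| Variant | Result |
|---|---|
| One-sided 5%, d = 0.5 | power 0.80; 70 per arm needed for 0.90 |
| One-sided 5%, d = 0.25 | power 0.34; 275 per arm needed for 0.90 |
| One-sided 5%, d = 0.5, 80% power | 51 per arm, close to 50, but not at the stated power |
| Rank-test efficiency 0.955, d = 0.5 | power 0.68 |
| Pilot added (55 per arm), two-sided | 0.74 for d = 0.5; about 0.26 for d = 0.25 |
| f² = 0.25 | 46 in total |
| η² = 0.25 | 34 in total |
| ANCOVA, f = 0.25 | 50 per arm only if the covariate–outcome correlation is about 0.64 |

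**Averaging T1 and T2.** With d = 0.5 at each time point and correlation ρ between them, the mean of the two has variance σ²(1 + ρ)/2. The noncentrality for F is λ = 2Nf²/(1 + ρ), on 1 and N − 2 degrees of freedom. With N = 100 and f = 0.25, λ = 12.5/(1 + ρ):

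| ρ | Power at N = 100 | N for 0.90 |
|---|---|---|
| 0 | 0.94 | 88 |
| 0.15 | 0.90 | 100 |
| 0.2 | 0.89 | 104 |
| 0.3 | 0.87 | 112 |
| 0.5 | 0.82 | 130 |
| 0.7 | 0.77 | 146 |

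Power falls to 0.90 at ρ = 0.166. The averaged score then has a standardised difference of 0.5/√0.583 = 0.655, the detectable difference found above.

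**Group-by-time interaction, f = 0.25.** Here λ = 2Nf²/(1 − ρ). The total needed is 88 at ρ = 0 and 46 at ρ = 0.5, so 100 does not come out without an unstated inflation. This test would also answer a different question. There is no IMS before the intervention, and T1 and T2 follow two different conversations, so the interaction asks whether the TM effect differs between them.

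**Attrition.** If 15% gave no outcome (an assumption), about 42.5 per arm would remain, and single-time-point power for d = 0.5 would be 0.62.

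**The case against.** The strongest reply is that the single-time-point t-test is not the document's choice. No test is fixed, the IMS is measured twice, and a two-group ANOVA over both measurements at f = 0.25 does reach 0.90 with 100 participants if the correlation is low. A low correlation is not absurd, because the two conversations are held with different staff about three weeks apart. Covariates and pilot data could help as well. At N = 100, power is 0.90 with ρ = 0.3 if covariates explain 10% of the variance, or with ρ = 0.5 if they explain 22%. If the pilot adds 10 participants, ρ = 0.3 is enough without covariates. The calculation is called preliminary, and the article is a condensed account.

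Part of this stands:

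- The d = 0.25 reading fits the word moderate poorly, so about 70% is the fairer headline than 24%.
- If the analysis does average T1 and T2, the relevant range is about 0.77 to 0.89 at correlations of 0.7 to 0.2, before covariates.
- The IMS sentence can be read as showing only that the scale is able to detect differences.

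The rest does not rescue the claim. Every route to 0.90 needs a correlation or a share of explained variance that the document does not state. No baseline IMS is described, so covariates would have to be cognition, function and demographics, whose strength is unknown. Averaging also assumes the same TM effect in both conversations. As for the calculation being preliminary, it is the only basis given for the sample size, and inclusion began in November 2022 (Time plan). Condensing can explain a missing test name, but it does not make the stated numbers agree.

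**Conclusion.** The concern holds. For the two-arm comparison that RQ1 and RQ2 ask for, 50 per arm does not give 0.90 power at an effect size of 0.25. On the more favourable and more natural reading (f = 0.25, d = 0.5), power is about 0.70 and 86 per arm are needed. On the other (d = 0.25), power is about 0.24 and 338 per arm are needed. One-sided testing, a rank test or pooling the pilot does not bring either reading to 0.90.

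These figures assume a two-sided 5% test, equal arms, one outcome per participant, no covariate adjustment and no attrition. A repeated-measures average does better, but reaches 0.90 without covariates at N = 100 only if the T1–T2 correlation is about 0.17 or lower, which is nowhere stated.

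**What to change.** Keep 100 participants and restate the sample-size paragraph under Recruitment and eligibility criteria:

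1. Name the effect-size metric, the test and the sidedness.
2. Give the power that 50 per arm provides. For an unadjusted comparison at one time point this could read: with 50 per arm and a two-sided 5% test, the trial has 90% power for a standardised between-arm difference of 0.65 and 80% for 0.57; power for a difference of 0.5 is 70%.
3. If the intended analysis averages T1 and T2 or adjusts for covariates, say so instead. State the assumed correlation and explained variance with their source, and show power over a range, for example 0.89, 0.82 and 0.77 at correlations of 0.2, 0.5 and 0.7 for f = 0.25 without covariates.
4. Do not offer the over-time result in 18 people as support for the sample size. Removing it from this paragraph is simplest; presenting it only as evidence about the scale would also do.

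The cost is wording. No participants are added and nothing changes in the conduct of the trial, but the stated power becomes less favourable.
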